## **PET Acquisition**

Participants will fast 4-6 hours before PET. An intravenous line will be placed 10-15 minutes prior to injection of 370 MBq FDG. Uptake of FDG will proceed while subjects are supine with eyes open in a quiet, dimly lit room. Scans will be performed 40 minutes post FDG injection using the CTI/Siemens (Siemens Corp, Hoffman Estates, IL) HR+ tomograph (63 image planes).

## **Data Analysis**

PET data will be analyzed by the statistical parametric mapping method of Friston and colleagues [11] to assess the main hypothesis of differences in HT randomization groups. Briefly, images from all subjects will be co-registered and reoriented into a standardized coordinate system using the SPM8 software package courteously provided by the Wellcome Department of Cognitive Neurology, Functional Imaging Laboratory (London). Data will be spatially smoothed, and normalized to mean global activity as previously described [12], except that an 8mm smoothing filter will be applied to images prior to statistical analysis. The set of pooled data will then be assessed with the t-statistic on a voxel-by-voxel basis, to identify the profile of voxels that significantly differed between subject groups. Brain regions considered appropriate for examination a priori, based upon well-established metabolic involvement in the earliest stages of prodromal Alzheimer's disease, are the bilateral precuneus/posterior cingulate areas, parietotemporal cortex in the vicinity of the angular and marginal gyri; medial prefrontal cortex, given its aging-related metabolic decline; and the medial temporal including the hippocampal area, inferior lateral temporal, and dorsolateral prefrontal cortex, for their roles in cognitive processes vulnerable to early decline in aging individuals [13, 14]. To statistically protect against multiple comparisons across the volume of the brain, a Bonferroni-type correction will be applied to twelve (left and right) regions specified by the a priori hypotheses, and group difference in those regions were noted if  $p < 0.05$  after correction; differences in other regions will be described here when  $p < 0.0005$  before adjustment. A number of analyses will be completed after stratifying the subjects according to estrogen HT formulation and various clinical variables, such as presence of APOE-4.

Clinical, demographic, and neuropsychological data will be analyzed using SPSS software version 13.0 (SPSS Inc., Chicago, IL). Two-group t-tests and chi-square tests will be used to assess any potential differences in clinical or demographic variables in the two subject groups (HT continuation or HT discontinuation). Paired t-tests will be used to assess changes in neuropsychological test performance between HT randomization groups to allow for consideration of correspondence with regional cerebral metabolism changes. Significance for

these analyses will be set at  $p < .05$  level without Bonferonni correction, given the small sample sizes and exploratory nature of these analyses. Further analyses will be conducted to assess differences according to estrogen HT formulation.

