## **PROTOCOL**

### **Subject Recruitment**

According to the enrollment schedule, subjects recruited during project year 1 will be followed through project year 3; those recruited during year 2 will be followed through year 4; those recruited during year 3 will be followed through year 5. Over the 5-year study period, we will need to retain 50 subjects to achieve the effect size of 0.80. To reach the desired effect size, we will screen by phone approximately 250 subjects (83 subjects per year). We anticipate that 102 subjects will meet preliminary inclusion criteria and will be scheduled for the initial visit (34 subjects per year) and we expect to randomize approximately 71 subjects who meet full inclusion criteria (24 subjects per year), bearing in mind expected rate for the telephone screening (60%), failure to meet inclusion criteria at initial visit (30%) and attrition due to withdrawal from the study either by the PI or by the subject herself (30%). We estimate a 70% rate of subject inclusion in the current proposal based on: a) growing concern on the side of physicians and women alike of the utility of long-term estrogen use in postmenopause; b) interest in definition of the risk for cognitive decline among postmenopausal women and c), brain imaging procedures (in her previous studies, the PI had encountered sustained interest in participation in the studies involving PET imaging to predict possible AD).

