### **Subject Participation**

In the present study, participants will be randomly assigned to continue or discontinue their existing estrogen hormone therapy (HT) for the duration of the 2-year study. The assessment schedule includes: a) screening and identification of subjects who meet inclusion criteria; b) clinical evaluation and blood drawing for general chemistry and other analyses; c) baseline neuroimaging (MRI, PET) and neuropsychological assessments; d) interim assessments; and e) two-year follow-up assessments. All tests performed at baseline will be repeated at a 2-year follow-up. Interim assessments with subjects in between in-person visits will include telephone contact at least every other month. At each three-month interval subjects will be asked to return for a follow-up visit to evaluate their general well-being, overall functioning, and subjective memory performance. Subjects will also be encouraged to contact the research team as needed.

Psychiatric examination. The baseline psychiatric assessment includes a psychosocial history, Structured Clinical Interview for DSM-IV--Patient Edition (SCID), and mental status examination,

and will take approximately hours to complete. [name] will oversee the clinicians that perform the psychiatric assessments and evaluate interrater reliability.

The following standardized rating scales and questionnaire will be used:

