The proposed research will help to define guidelines for estrogen use among postmenopausal women. Specifically, it will provide information regarding the effects of discontinuation from estrogen use on cognitive functioning.

Importance of the Knowledge to be Gained. There is little risk to participating in a study assessing the effects of continuation/discontinuation of estrogen use. Yet there is much to gain from identifying changes in brain metabolism and cognitive function, which may result from discontinuation of estrogen use.

- a) Individual: Subjects will receive a detailed psychiatric, physical, and neurological examination, including laboratory and cognitive assessment, and neuroimaging.
- b) Societal: Results of the study may further understanding of the possible protective effects of estrogen from cognitive decline.

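### The main PET test names no baseline, change or time term, although each woman is to be scanned twice; the contrast should be the year-2 group difference adjusted for the baseline scan

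*Protocol*

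**What the plan says.** Under Subject Participation, "participants will be randomly assigned to continue or discontinue their existing estrogen hormone therapy (HT) for the duration of the 2-year study". The assessment schedule there lists "baseline neuroimaging (MRI, PET) and neuropsychological assessments" and adds that "All tests performed at baseline will be repeated at a 2-year follow-up". Each woman who completes the study therefore has two FDG-PET scans.

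The paragraph on the importance of the knowledge to be gained, under Adequacy of Protection Against Risks, puts the purpose as "identifying changes in brain metabolism and cognitive function, which may result from discontinuation of estrogen use".

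The Data Analysis section assigns the main hypothesis, a difference between the randomised groups, to statistical parametric mapping. After co-registration, smoothing and normalisation to global activity, the test is described in one sentence: "The set of pooled data will then be assessed with the t-statistic on a voxel-by-voxel basis, to identify the profile of voxels" that differ significantly between the groups. A Bonferroni-type correction then covers twelve a priori regions at 0.05. No time point, change image, group-by-time term or baseline covariate is named. The only hint that change in PET is computed is in the later sentence on neuropsychological tests, which mentions relating test changes to changes in regional metabolism.

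On size, Subject Recruitment says "we will need to retain 50 subjects to achieve the effect size of 0.80" and "we expect to randomize approximately 71 subjects who meet full inclusion criteria".

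**The concern.** The section fixes the main test down to the software version, the filter width, the test statistic and the number of regions. It leaves open what the statistic is computed on. Three readings fit the wording: year-2 scans only, both scans of every woman together, or change images. They have different expected differences, different variances and, in one case, a different false-positive rate. With the text as it stands, the choice could be made after the scans have been seen.

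Power is also at stake. The trial expects about 25 evaluable women per arm and tests twelve regions with correction. The baseline scan is the one source of added precision that costs nothing more to collect, and the stated test does not say that it is used.

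**Working it through.** **Inputs from the protocol.** 50 women retained, effect size 0.80, about 71 randomised, 30% attrition (Subject Recruitment); Bonferroni over twelve regions, so 0.05/12 = 0.00417 per region (Data Analysis).

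**Assumptions, because the protocol does not state them.** 1:1 allocation (25 per arm); two-sided testing; 80% power as the planning target; 0.80 in SD units of the year-2 scan; equal SD at both times; baseline-to-year-2 correlation r, varied from 0.3 to 0.8.

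**Step 1: reproduce the protocol's figure.** With the normal approximation, n per arm = 2(1.960 + 0.842)² / 0.80² = 24.5, so 25 per arm and 50 in all. Also 71 × 0.70 = 49.7. The figure of 50 thus fits an unadjusted comparison of one value per woman at an uncorrected 0.05. The exact t calculation gives 79% power at 25 per arm. At 0.05/12 the same formula gives 2(2.865 + 0.842)² / 0.80² = 42.9, so 43 per arm and 86 in all.

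**Step 2: expected difference and variance under each reading.** Variance is relative to that of a single scan. The noncentrality is (difference / √variance) × √(25/2).

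- Year-2 scans only: difference 0.80, variance 1. Noncentrality 0.80 × 3.536 = 2.83.
- Year-2 scans with baseline as covariate: difference 0.80, variance 1 − r², 47 degrees of freedom. At r = 0.7: 0.80/√0.51 × 3.536 = 3.96.
- Change score, which is what a group-by-time contrast on two scans amounts to: difference 0.80, variance 2(1 − r). At r = 0.3: 0.80/√1.4 × 3.536 = 2.39.
- Both scans averaged per woman: randomisation makes the expected baseline difference zero, so the difference is (0 + 0.80)/2 = 0.40, with variance (1 + r)/2. At r = 0.5: 0.40/√0.75 × 3.536 = 1.63.

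**Step 3: power at two-sided 0.05/12, noncentral t, 25 per arm.**

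| r | Year-2 only | Year-2, baseline as covariate | Change score | Mean of both scans |
|---|---|---|---|---|
| 0.3 | 44% | 49% | 28% | 12% |
| 0.5 | 44% | 60% | 44% | 10% |
| 0.6 | 44% | 70% | 56% | 9% |
| 0.7 | 44% | 82% | 74% | 8% |
| 0.8 | 44% | 95% | 92% | 8% |

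The covariate analysis is better than year-2 only at every r shown. The change score equals year-2 only at r = 0.5, since 2(1 − 0.5) = 1, and is worse below that.

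**Step 4: pooled scans treated as independent.** The variance of the group difference is then understated by a factor of 1 + r, so the test statistic is too large by √(1 + r). In large samples the false-positive rate at a nominal 5% is 2[1 − Φ(1.960/√(1 + r))], which is 11% at r = 0.5 and 14% at r = 0.8. At a nominal 0.42% the same formula with 2.865 gives 1.9% and 3.3%.

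**The case against.** A reader might infer that the protocol discards the baseline scan. It does not say so. Pooled is undefined and may simply mean images from all subjects, and a difference between groups is as compatible with change images as with year-2 images. The remark about changes in regional metabolism suggests that some change measure was in mind. This stands, so the finding is that use of the baseline is not stated.

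A reader might also infer that a year-2 comparison would fail to test the effect of randomisation. That does not follow. Randomisation makes it a valid test, apart from dropout, which baseline adjustment does not in general cure. Chance baseline imbalance is already covered by the stated significance level, so on that reading the loss is one of precision.

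Nor should the 44% be read as the cost of leaving out the baseline. The same year-2 test has 79% power at 0.05; the fall comes from the twelve-region correction, which is a separate sample-size matter. The gains also depend on r, and would differ if 0.80 already refers to change.

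Finally, covariates and design details are often left to a statistical analysis plan, and none was available for this review. That carries less weight here. The protocol does specify the main test, in detail, and the missing element decides what is being compared.

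**Conclusion.** The point holds as a defect in how the main contrast is specified, with a better method available from data already planned. As written, the main PET test is a between-group t-statistic with no baseline, change or time term, in a trial that scans each woman twice and aims at change.

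Under the assumptions listed, adjusting for baseline raises power at the corrected level by about 5 percentage points at r = 0.3, 16 at r = 0.5 and 38 at r = 0.7. Pooling both scans would be much worse than any other reading: half the expected difference, and invalid p-values if the pairing is ignored. The documents do not show which reading is intended, and they give no value of r, so the size of the gain is a range. Its direction is not in doubt over the correlations examined. The change should be made, but the finding does not show the planned comparison to be invalid.

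**What to change.** In Data Analysis, replace the sentence on pooled data with a defined contrast: the randomised-group difference in year-2 uptake, with the same voxel's or region's baseline uptake as covariate. Use that contrast for the twelve a priori regions. State that each woman contributes one year-2 value and one baseline value, so that no analysis treats her two scans as independent.

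A group-by-time or change-score contrast should not be offered as the minimum acceptable alternative, because it gains nothing over the year-2 comparison at r = 0.5 and loses power below it. If the investigators do mean change images, the text should say so and give the correlation on which that choice rests.

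The cost is wording and some analyst time. For the twelve regions the analysis is an ordinary regression; the voxel map may need additional set-up to take a voxel-specific covariate. No further subjects, visits or scans are needed.

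### The main PET test is made voxel by voxel but corrected only for twelve regions, so as written the rule does not control false positives within those regions or across the brain

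*Protocol*

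**What the plan says.** All of this is in the first paragraph of the protocol's Data Analysis section.

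- **Purpose.** The PET analysis is run "to assess the main hypothesis of differences in HT randomization groups".
- **Unit of testing.** "The set of pooled data will then be assessed with the t-statistic on a voxel-by-voxel basis". No other unit is named.
- **Smoothing.** "an 8mm smoothing filter will be applied to images prior to statistical analysis".
- **Aim of the correction.** The stated aim reads "To statistically protect against multiple comparisons across the volume of the brain".
- **Rule in the prespecified regions.** The means chosen is that "a Bonferroni-type correction will be applied to twelve (left and right) regions specified by the a priori hypotheses".
- **Criterion for reporting such a region.** The threshold is worded as "group difference in those regions were noted if $p < 0.05$ after correction".
- **Rule elsewhere.** For the rest of the brain the text says that "differences in other regions will be described here when $p < 0.0005$ before adjustment".

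The section mentions no regional mean, small-volume correction, random-field or false-discovery-rate correction, or minimum cluster size. The next paragraph calls the clinical and neuropsychological tests exploratory and leaves them uncorrected. The PET tests carry no such label.

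**The concern.** A divisor of twelve is right when twelve tests are made. A voxel-wise map makes many correlated tests inside each region, and the region is reported if any of its voxels passes. Dividing 0.05 by twelve then covers the choice among regions but not the choice of the best voxel within a region. Outside the twelve regions no correction is applied, although the sentence opens by promising protection over the whole brain volume.

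This is the rule for the trial's main hypothesis. If it is followed literally, a regional difference between the continuation and discontinuation groups could be reported as significant after correction when its real error rate is many times 5%.

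**Working it through.** **Inputs from the protocol.** Twelve regions; 0.05 after correction; 0.0005 unadjusted elsewhere; an 8 mm filter; 50 women retained (Subject Recruitment), hence 48 degrees of freedom for two groups.

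**Assumptions, not in the protocol.** Region volume, total smoothness (FWHM; the 8 mm filter is a lower bound because scanner resolution adds to it), brain volume, equal arms, and sidedness, which is not stated.

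**1. The plan's own figure.** Six named areas × two sides = 12. With one test per region, 12 × 0.05/12 = 0.05; for independent tests, 1 − (1 − 0.05/12)^12 = 0.049. The arithmetic is correct for twelve tests.

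**2. Best voxel per region judged at 0.05/12 = 0.00417, random-field calculation.** One-sided, 48 df, t = 2.75. The expected Euler characteristic is E = Σ R_d ρ_d(t). At this t the densities are ρ0 = 0.00417, ρ1 = 0.00847, ρ2 = 0.01541 and ρ3 = 0.02399. For a sphere of radius r in FWHM units, R = (1, 4r, 2πr², 4πr³/3). The region error is 1 − exp(−E), and over twelve independent regions 1 − exp(−12E).

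- Small, smooth case (5 cm³, 15 mm): r = 0.707, R = (1, 2.83, 3.14, 1.48). E = 0.004 + 0.024 + 0.048 + 0.036 = 0.112. Region error 10.6%; over twelve, 1 − exp(−1.345) = 74%.
- Large, rough case (20 cm³, 8 mm): r = 2.105, R = (1, 8.42, 27.84, 39.06). E = 0.004 + 0.071 + 0.429 + 0.937 = 1.441. Region error 76%; over twelve, nearly 100%.

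**3. Check by simulation.** Null Gaussian fields, 2 mm voxels, cubes of 16, 20 and 26 mm (4.1, 8.0 and 17.6 cm³), FWHM 8, 12 and 14 mm, two-sided at 0.05/12, 1,500 fields per setting.

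| FWHM | 16 mm cube | 20 mm cube | 26 mm cube |
|---|---|---|---|
| 8 mm | 27% | 44% | 70% |
| 12 mm | 12% | 21% | 39% |
| 14 mm | 11% | 17% | 30% |

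The lowest cell is 10.9%, so over twelve independent regions 1 − (1 − 0.109)^12 = 75%. The sampling error of that cell is about √(0.109 × 0.891/1500) = 0.8 percentage points, so this does not differ from the 74% above. A separate simulation of two-sample t-fields with 25 per arm (18 and 24 mm cubes, 8–15 mm) gave 16–58% per region one-sided.

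**4. Dependence between regions.** If all twelve regions were perfectly correlated, the family-wise error would equal the single-region error, which is still at least about 10%, twice the nominal 5%.

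**5. Rest of the brain at p<0.0005.** One-sided z = 3.29. Expected false clusters = (V/FWHM³)(4 ln 2)^1.5 (2π)^−2 (z² − 1) exp(−z²/2).

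- 1200 cm³ at 14 mm: 437 resolution elements, 2.2 clusters.
- 1400 cm³ at 8 mm: 2734 resolution elements, 14.0 clusters.

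Removing the twelve regions, at most 12 × 18 = 216 cm³, lowers the first figure to about 2.2 × 984/1200 = 1.8. For comparison, whole-brain family-wise control at 0.05 would need a voxel p of about 4 × 10⁻⁶ to 3 × 10⁻⁷ (t about 5.0–5.7; 1.0–1.4 litres, 8–15 mm, 48 df, one-sided).

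**The case against.** The strongest reply is that the protocol applies its correction to regions and never says that a raw voxel p-value is multiplied by twelve. SPM8 can produce a small-volume-corrected p-value per region. If that, or one regional mean, was meant, 12 × 0.05/12 = 0.05 is exact. The within-region unit might also be set out in a statistical analysis plan, which is not available here. This stands to the extent that the text does not explicitly fix the unit. A reader might infer that protection within the regions is certainly absent; the document does not support that. But the only unit it names is the voxel, and the other readings need a step that it does not mention.

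Second, differences elsewhere are only to be described, and the threshold is openly unadjusted. That stands too: 0.0005 is acceptable as a descriptive screen, and the text does not call it corrected. What remains is that it sits under an opening promise of protection over the whole brain.

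Third, region size, smoothness, brain volume and independence are all assumed. They move the per-region error from about 10% to about 70%, and positive correlation between regions lowers the family-wise figure. No setting examined, including full correlation, brings it down to 5%.

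**Conclusion.** The point holds as a defect in the stated rule. On the natural reading, the main PET test has a false-positive rate of about 10–70% per region and about 74% to nearly 100% over twelve independent regions (at least about 10% under full correlation), against the intended 5%. These figures assume regions of about 4–18 cm³ and smoothness of 8–14 mm, and that any voxel in a region may qualify.

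If one value per region is tested, the correction is valid inside the twelve regions. The claim about the whole brain volume is still untrue, since about 2–14 false clusters per one-sided contrast would be expected at p<0.0005 over an assumed 1200–1400 cm³.

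A reader might go further and conclude that a positive PET result would carry almost no evidence. The document does not support that: it would depend on the unit actually used, the observed p-values and the extent of the finding. The supportable statement is that, as written, a positive result cannot be credited with the 5% error rate that the plan implies.

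**What to change.** In Data Analysis, state the unit of testing in the twelve prespecified regions and match the correction to it, in one of two ways:

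1. Extract one prespecified mean normalised uptake per region and test the twelve values with Bonferroni or Holm at an overall 0.05.
2. Keep the voxel map and require a small-volume family-wise corrected p below 0.05/12 within each region, as SPM8 allows.

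Limit the error-control claim to those twelve regions. State that differences elsewhere at p<0.0005 are descriptive and support no inference unless they also reach whole-brain family-wise p<0.05.

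The change is to wording and analysis only, with the same scans and software. The price is that fewer regions will be declared positive. As a guide, if the protocol's effect size of 0.80 applied to a single regional mean with 25 women per arm, the normal approximation gives power Φ(0.80 × √12.5 − 2.865) = 48.5% at two-sided 0.05/12, against Φ(0.80 × √12.5 − 1.960) = 80.7% at 0.05.

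### Stratifying by HT formulation and APOE-4 is the only subgroup method named, and on its natural reading it does not test whether the effect of discontinuing HT differs between strata

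*Protocol*

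**What the plan says.** All statements on subgroups are in the protocol's Data Analysis section.

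- **PET.** The main hypothesis is a difference between the randomised groups. The pooled images are "assessed with the t-statistic on a voxel-by-voxel basis, to identify the profile of voxels that significantly differed between subject groups". For multiplicity, "a Bonferroni-type correction will be applied to twelve (left and right) regions specified by the a priori hypotheses"; other regions are described at p < 0.0005 unadjusted. The paragraph ends by saying that "analyses will be completed after stratifying the subjects according to estrogen HT formulation and various clinical variables, such as presence of APOE-4".
- **Clinical and neuropsychological data.** The tests named are two-group t-tests, chi-square tests and, for change in test performance, paired t-tests. The level is .05 without correction, and these analyses are called exploratory. The section ends: "Further analyses will be conducted to assess differences according to estrogen HT formulation".

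None of the tests named contains an arm-by-factor term. On size, Subject Recruitment states that "we will need to retain 50 subjects to achieve the effect size of 0.80".

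**The concern.** Asking whether the effect differs by formulation means asking whether the continue-minus-discontinue contrast is the same for all formulations. A comparison of arms inside one stratum has a different null hypothesis: no arm difference in that stratum. Two such tests can disagree on significance while the two effects are identical, simply because each uses only part of a small sample.

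The statement of potential benefits says the research should help to define guidelines for estrogen use. That sentence concerns discontinuation and cognition in general. Even so, a result of the form 'significant with one formulation, not with another' would invite a conclusion about formulation that no named test supports. The number of stratifying variables is left open, which gives more chances for such a pattern to appear.

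**Working it through.** **Inputs from the protocol.** 50 women retained, effect size 0.80 and 30% attrition (Subject Recruitment); 12 a priori regions with Bonferroni-type correction, and .05 uncorrected for clinical and neuropsychological data (Data Analysis).

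**Assumptions.** 0.80 is a standardised mean difference; allocation is 1:1; tests are two-sided; there are two strata, balanced by arm. Stratum shares are not given, so a range is used.

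**1. The plan's own figure.** Assuming alpha 0.05 and 80% power, n per arm = 2(1.960 + 0.842)² / 0.80² = 24.5, rounded up to 25, or 50 in total. This matches. The noncentral t gives 79.1% power at 25 per arm. About 71 randomised with 30% lost leaves 71 × 0.70 = 49.7, also consistent.

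**2. Same true effect of 0.80 in both strata.** Power in each stratum comes from the noncentral t with m women per arm, df = 2m − 2 and noncentrality 0.80/√(2/m). The chance that exactly one stratum is significant is p₁(1 − p₂) + p₂(1 − p₁).

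| Split of the 50 | Per arm | Power at .05 | Exactly one, .05 | Power at 0.05/12 | Exactly one, 0.05/12 |
|---|---|---|---|---|---|
| 50/50 | 12.5 / 12.5 | 48.3% / 48.3% | 49.9% | 14.9% / 14.9% | 25.4% |
| 40/60 | 10 / 15 | 39.5% / 56.2% | 51.3% | 10.2% / 20.3% | 26.3% |
| 30/70 | 7.5 / 17.5 | 30.0% / 63.2% | 55.3% | 6.1% / 26.0% | 28.9% |
| 20/80 | 5 / 20 | 20.1% / 69.3% | 61.6% | 3.0% / 31.9% | 33.0% |

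For the first row at .05: 2 × 0.483 × 0.517 = 0.499. At 0.05/12 = 0.00417: 2 × 0.149 × 0.851 = 0.254. Half-integer stratum sizes are a convenience. Simulation (40,000 trials) with whole numbers at .05 gives 50.3% for 12/13 per arm and 54.1% for 8/17.

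**3. Smaller common effect.** With 0.50 in both strata and splits from 50/50 to 30/70, exactly one is significant in 34.8-35.9% at .05 and 8.1-8.8% at 0.05/12.

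**4. No effect in either stratum.** At .05: 2 × 0.05 × 0.95 = 9.5%. At 0.05/12: 2 × 0.00417 × 0.99583 = 0.8% per region.

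**5. Interaction test.** The contrast is the difference between the two stratum effects, with SE = √(2/m₁ + 2/m₂) in SD units. Tested at .05 in the same simulations, it rejects in 4.8-5.1% of trials, whether the common effect is 0.80 or zero.

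**6. What the interaction test can detect (normal approximation, .05).**
- 50/50: SE = √(2/12.5 + 2/12.5) = 0.566. Power for an interaction of 0.80 SD is Φ(0.80/0.566 − 1.960) = 29%. For 80% power the interaction must be 2.802 × 0.566 = 1.58 SD.
- 30/70: SE = √(2/7.5 + 2/17.5) = 0.617. Power is 25%; 80% power needs 1.73 SD.

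**The case against.** The strongest reply is that the protocol does not prescribe the faulty inference. Four parts of it deserve an answer.

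- **Re-testing within strata is not written.** A reader might infer that the protocol commits to repeating the arm comparison in each stratum and judging strata by which p-values pass. It says only that analyses follow stratification, and the closing sentence on formulation names no test. This stands, so the point rests on the natural reading. That reading is well grounded: the sentence directly follows the voxel-wise comparison of groups and its thresholds, and no other subgroup method appears.
- **APOE-4.** A reader might infer a stated question about whether the effect differs by APOE-4. The text gives that aim for formulation only; APOE-4 appears only as an example of a stratifier. This stands, so for APOE-4 the point is conditional on a difference being claimed.
- **The 50% figure.** A reader might take it as the size of the problem for PET. The stratification sentence belongs to the PET paragraph, where the a priori regions are judged after correction over twelve, so 25-29% per region is the relevant figure there. The .05 figure is for a two-group test; the paired t-test named for cognitive change was not modelled. The effect size of 0.80 is also tied to no named outcome.
- **The statistical analysis plan.** An interaction test may be specified there, so its absence from the protocol alone is no finding. The remaining point is narrower: the protocol names one method and one aim, and on the natural reading the first does not serve the second.

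The exploratory label softens the matter for the clinical and neuropsychological analyses. It does not clearly extend to the stratified PET analyses.

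**Conclusion.** The concern holds in this limited form. Stratification is the only subgroup method named, an aim to assess differences by formulation is stated, and arm comparisons within strata would not test such a difference.

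Given a common effect of 0.80, 50 evaluable women, 1:1 allocation and two strata split between 50/50 and 30/70, discordant significance arises in about 25-29% of trials per a priori region at 0.05/12, and in about 50-55% for a two-group test at .05. A more uneven split raises these figures and a smaller common effect lowers them. With no effect they are 0.8% and 9.5%. Discordance becomes an error only when it is read as effect modification. The protocol does not adopt that reading, but it offers no other basis for a claimed difference. The main comparison of the randomised groups is not affected.

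**What to change.** Amend the Data Analysis section as follows:

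- Base any claimed difference by formulation, and by APOE-4 if one is claimed, on an arm-by-factor interaction in all women with evaluable data.
- For PET, fit it as a contrast in the existing SPM model or on the a priori regional values. For cognition, fit it to the change score of each neuropsychological test, since the protocol defines no single score.
- Report the interaction estimate with its 95% confidence interval and label it exploratory.
- Show stratum-specific results as description only, and draw no conclusion from significance in one stratum and not in another.

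The cost is a change of wording and an added interaction contrast on data that are already to be collected; no further women or visits are needed. If regional values are used, they must also be extracted. The real drawback is low power: about 25-29% for an interaction of 0.80 SD at .05, and less at a corrected threshold. Most such results will be inconclusive and should be reported as such.
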